### Study participants and measurements

All patients will be selected from the outpatient renal clinic of five tertiary hospitals in Korea (Seoul National University Bundang Hospital, Seoul National University Hospital, Seoul National University Boramae Medical Center, Gachon University Gil Hospital, and Wonju Severance Christian Hospital). Patients aged 20 to 75 years who are on PD and have a daily urine output of more than 500 ml will be screened
[7]. The following tasks will be conducted at the initial visit: 1) completion of questionnaire on medical and drug history, including the use of anti-hypertensive medication and diuretics; 2) physical examination of all body systems; 3) measurement of height and weight with an empty abdomen; and 4) BP and pulse rate measurement. Participants who meet all of the inclusion and exclusion criteria and who provide written informed consent will be eligible for this study.

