### Randomization

The randomization process will be conducted using a web-based computer program. A list of random numbers will be generated by a computerized random allocation system operated by the Medical Statistics Support Team in Seoul National University Hospital. Eligible participants will be randomly assigned 1:1 to either the control group (fluid management based on the clinical information alone) or treatment group (BIS-guided fluid management along with clinical information). Randomization will be stratified based on the institution and presence of diabetes mellitus, and will utilize a randomized block design.

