### Outcome measures

The primary outcome is the change in GFR between months 0 and 12 after starting treatment. The secondary outcomes will include GFR measured by urine collection, calculated by the mean of the Cr and urea clearance at month 12; time to the anuric state (urine volume <100 ml/day); and fatal and nonfatal cardiovascular events, including acute myocardial infarction, stroke, unstable angina, and cardiovascular revascularization. Parameters obtained by echocardiographic measurements, such as the left ventricular mass index, E/e′ ratio, left ventricular end-diastolic pressure, left ventricular ejection fraction, left atrial volume index, and BP at month 12; parameters measured by BIS, such as the OH value, ECW, and ECW/ICW; hospitalization, cardiovascular and all-cause mortality, and transfer to HD over the course of 1 year; pulse wave velocity (PWV), type and number of PD fluid and diuretics at month 12, and laboratory findings including high-sensitivity C-reactive protein (hs-CRP), N-terminal prohormone of brain natriuretic peptide, and cardiac troponin T, will also be evaluated as tertiary outcomes.

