### Statistical analyses

The statistical analyses will be conducted both on a per-protocol (PP) and an intention-to treat (ITT) basis. For PP analysis, all participants who complete the study will be included to evaluate the primary and secondary outcomes. For the ITT analysis, all participants who are enrolled and randomized to one of the two groups and who complete the first visit will be included.

Basic statistics will be reported in terms of mean ± SD for continuous variables, or as percentages for categorical variables. Differences between groups will be analyzed using Student’s *t*-test for continuous variables and the *χ*^2^ test or Fisher’s exact test for categorical variables. The difference in GFR between month 0 and month 12 will be compared between the two groups using Student’s *t*-test for the primary outcome. Analysis of covariance (ANCOVA) will be used to analyze the primary outcome as the secondary analysis to adjust the baseline value. Multivariate Cox proportional hazard regression models will be used to analyze the time to development of anuria. Although the institutions are mainly located in large cities, thereby limiting the likelihood of any important cluster effect, we will be sure to accommodate possible clustering in our models and analysis as required. A value of *P* < 0.05 will be considered statistically significant. All analyses will be performed using SPSS Statistics software (v21.0; IBM Corporation, Armonk, NY, USA).

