[23–25]. Although some studies have suggested cutoff thresholds for the definition of the OH in patients on HD and patients on PD of 2.5 and 2.0 liters, respectively
[19, 26, 27], we consider an ECW within ±1.1 liter as normal hydration.

There is a chance that patients within the same institution will be more correlated than patients between institutions. To avoid this, we will investigate for possible clustering of patients at the recruitment institution level, and will accommodate such clustering in our models and analysis as required. We also conservatively calculate the sample size, assuming a high drop-out rate, to overcome this potential problem.

A limitation of this study is that we will include both prevalent and incident patients on PD. Although a study targeting only incident patients on PD might provide more solid results, we will adjust the dialysis vintage in the multivariable analyses.

In summary, the COMPASS study is the first prospective, randomized controlled trial to evaluate the clinical usefulness of BIS-guided fluid management in patients on PD. The aim of this study is to evaluate whether BIS-guided fluid management has a beneficial effect on the decline of RRF, cardiac parameters, and cardiovascular outcomes.

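### Randomisation is stratified by institution and diabetes but the primary t-test uses neither, and the drop-out allowance is wrongly offered as protection against clustering

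*Protocol article*

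**What the plan says.** All references are to the protocol article.

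- **Randomization.** Allocation is individual: "Eligible participants will be randomly assigned 1:1 to either the control group" or the treatment group. "Randomization will be stratified based on the institution and presence of diabetes mellitus, and will utilize a randomized block design". Patients come from the "outpatient renal clinic of five tertiary hospitals in Korea" (Study participants and measurements), so there are 5 × 2 = 10 strata.
- **Outcome measures.** "The primary outcome is the change in GFR between months 0 and 12 after starting treatment".
- **Statistical analyses.** The change is compared between groups by "Student’s *t*-test for the primary outcome". ANCOVA "will be used to analyze the primary outcome as the secondary analysis to adjust the baseline value". Neither institution nor diabetes is named as a covariate. On institution, the section says "we will be sure to accommodate possible clustering in our models and analysis as required", without a criterion, a model form or a list of the analyses affected.
- **Discussion.** The team will look for clustering by recruiting institution and deal with it if needed. It then adds: "We also conservatively calculate the sample size, assuming a high drop-out rate, to overcome this potential problem". The problem meant is correlation among patients of the same institution.
- **Sample size calculations.** The drop-out allowance is 20% and is attributed to poor compliance.

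**The concern.** Three things do not fit together.

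1. **The analysis does not follow the randomisation.** Blocked randomisation within strata keeps the arms close to balanced on institution and diabetes, so differences between strata largely cancel from the treatment contrast. A t-test without those factors still counts the differences as noise in its standard error. If the strata are prognostic, the p-value is too large and the precision gained by stratifying is not used.

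2. **The role of institution is left open.** The conditional promise, read with the Discussion's plan to examine clustering, can be taken to mean that a model may change after the data have been inspected. In an open-label trial it should be plain that the primary analysis is not subject to this.

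3. **The sample-size reassurance does not hold.** An allowance made for patients who leave cannot also cover correlation among those who stay. The sentence also suggests that clustering threatens the sample size here as it would in a cluster-randomised trial, which is not so.

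**Working it through.** **Inputs from Sample size calculations:** one-year GFR change −16.8 (SD 19.9) and 0.09 (SD 40.9) l/week/1.73 m²; two-sided α = 0.05; power 80%; drop-out 20%; 69 per group.

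**Step 1. Reproduce the stated sample size.**
- Difference δ = 0.09 + 16.8 = 16.89.
- Pooled SD = √[(19.9² + 40.9²)/2] = 32.16.
- n per group = 2 × [32.16 × (1.96 + 0.8416)/16.89]² = 56.9, rounded up to 57.
- 57 × 1.2 = 68.4, rounded up to 69. This matches the protocol.

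**Step 2. Is any of the allowance spare?**
- With the planned loss, 69 × 0.8 = 55.2, so about 55 per group remain, fewer than the 57 required.
- SE = 32.16 × √(2/55) = 6.13, and δ/SE = 2.754.
- Power = Φ(2.754 − 1.96) = 78.6% (77.9% by noncentral t).
- Drop-out uses the whole allowance. Only if nobody dropped out (69 per group, about 87% power) would anything be left.

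**Step 3. Is a cluster inflation needed?** Take an intra-institution correlation of 0.05 (an assumption; the protocol gives none) and 138/5 = 27.6 patients per institution.
- If whole institutions were randomised: 1 + (27.6 − 1) × 0.05 = 2.33.
- With individuals randomised in balance within institutions: 1 − 0.05 = 0.95.

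The second case is this trial, and it needs no inflation.

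**Step 4. Effect of leaving the strata out of the test.** Let R² be the share of outcome variance explained by institution and diabetes together. The protocol gives no value, so a range is shown. Assume exact balance, a common SD of 32.16 and 55 per group. The t-test estimates SE = SD√(2/n), while the true standard error of the difference is SE√(1 − R²). Hence:
- true alpha of the t-test = 2[1 − Φ(1.96/√(1 − R²))]
- power, unadjusted = Φ[(2.754 − 1.96)/√(1 − R²)]
- power, adjusted = Φ[2.754/√(1 − R²) − 1.96]

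| R² | True alpha, t-test | Power, t-test | Power, adjusted |
|---|---|---|---|
| 0 | 5.0% | 78.6% | 78.6% |
| 0.05 | 4.4% | 79.2% | 80.7% |
| 0.10 (5% + 5%) | 3.9% | 79.9% | 82.7% |
| 0.20 (10% + 10%) | 2.8% | 81.3% | 86.8% |

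Example, R² = 0.10: √0.90 = 0.9487; 1.96/0.9487 = 2.066, giving alpha 3.9%; 0.794/0.9487 = 0.837, giving 79.9%; 2.754/0.9487 − 1.96 = 0.943, giving 82.7%.

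**Step 5. Simulation with imperfect balance.** Assumptions: 138 randomised, five institutions crossed with diabetes, permuted blocks of 4, 20% random loss. At 5% + 5%, t-test alpha is about 4.2% and power is 79% unadjusted against 82% adjusted. At 10% + 10%, alpha is about 3.2% and power is 80% against 87%. With no stratum effect, both analyses hold alpha near 5% and adjusting costs at most about one point of power. This agrees with the formulas, allowing for incomplete blocks and simulation error.

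**The case against.** **The harm is small and in the safe direction.** This stands. The unadjusted test keeps about 79% to 81% power over the whole range in Step 4, so what is lost is an available gain. Every figure depends on variance shares and a block size that the protocol does not give.

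**A reader might infer that institutional clustering inflates type I error, or that 138 should carry a design effect.** The documents do not support this. Individuals are randomised within institutions, and ignoring the strata takes alpha below 5%, not above it.

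**A reader might infer that the primary model will be picked after seeing the data.** That goes beyond the text. The t-test is stated without condition and ANCOVA is labelled secondary. The clustering sentence comes after the Cox models and does not say that the t-test would be replaced. What stands is that the wording permits the other reading and should be closed off.

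**Covariate lists may sit in a statistical analysis plan that is not shown.** This is fair for the detail of adjusted models, and the absence of diabetes from the article is weak evidence by itself. It does not answer the point, because the article itself fixes the unadjusted primary test and itself makes the drop-out argument.

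**A reader might infer that every secondary model needs the stratum terms.** That does not follow. Anuria and cardiovascular events over one year in 138 patients may be few, and five extra terms could make those models unstable.

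**Conclusion.** The point holds as a worthwhile improvement to the analysis; it is not a threat to validity. The primary test disregards the stratification and is therefore conservative whenever institution or diabetes predicts GFR change. Adjusting gains about 3 points of power at the 5% + 5% shares and about 6 to 7 points at 10% + 10%. These sizes rest on the assumed shares, a common SD of 32.16, blocks of 4 and loss at random.

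Two parts need no variance assumption. The drop-out allowance gives no cover for clustering, because the planned loss already leaves fewer patients than the calculation requires. And the conditional wording on clustering is ambiguous about whether it reaches the primary analysis.

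**What to change.** 1. Make the primary analysis of 12-month GFR change a prespecified ANCOVA with treatment, baseline GFR, institution (four indicator terms) and diabetes as fixed effects. Keep Student's t-test as a supporting analysis.
2. Remove the conditional wording, and the examination of clustering, as a trigger for the primary model. Clustering may still be described.
3. Delete the Discussion sentence that links the drop-out allowance to clustering.
4. Do not require all stratum terms in the secondary event models. Decide that by the number of events expected.

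**Cost.** No new data, no change in conduct and no larger sample. The strata use 4 + 1 = 5 of the 2 × 55 − 2 = 108 degrees of freedom that the t-test would have, which costs at most about one point of power if the strata explain nothing. The primary test would differ from the one used for the sample size. That should be stated openly, and the change should be made before any comparison of the groups is seen.

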### Ethics approval

The study will be performed in accordance with the Declaration of Helsinki, as amended by the 59th World Medical Association General Assembly in 2008. All the participants will provide signed, informed, written consent, stating that participation is voluntary and can be withdrawn at any time. Approval for the study has been obtained from the institutional review board of Seoul National University Bundang Hospital (E-1303/194-001), Seoul National University Hospital (H-1302-050-465), Seoul National University Boramae Medical Center (16-2013-30), Gachon University Gil Hospital (GAIRB2013-119), and Wonju Severance Christian Hospital (CR312065). The trial protocol has been registered at http://www.clinicaltrials.gov (NCT01887262).

## Discussion

Preservation of RRF has been shown to be associated with a reduction in mortality, and has become one of the prime objectives in the treatment of patients on PD
[14, 15]. Controversy remains about whether hypervolemia or strict volume control helps preserve RRF in these patients
[3, 16, 17]. Other groups have reported that BIS may be superior to clinical information in the assessment of fluid status for patients on HD or PD
[2, 9, 12, 18]. However, no studies have evaluated the effect of regular and serial BIS-guided fluid management on RRF in patients receiving PD. To our knowledge, this is the first multicenter, prospective, randomized controlled trial assessing whether BIS-guided volume management attenuates the loss of RRF. The endpoints of the COMPASS (Control Of fluid balance guided by body composition Monitoring in patients on PeritoneAl dialySiS) study are of the utmost importance to healthcare providers.

The strength of the study is that only subjects who are on PD for more than 1 month are eligible. This criterion reduces the likelihood of a pre-dialytic uremic factor confounding the primary outcome. Potential covariates, such as, the differences in treatment strategies between physicians, can also be minimized because physicians will prescribe PD solutions, diuretics, and diet according to the same protocol. Therefore, it is reasonable that the type and number of PD solutions and diuretics should serve as the secondary outcomes.

The OH value has been widely used in the assessment of volume status in patients on PD
[19–21]. Additionally, O’Lone et al. recently reported the clinical significance of the OH index, - an accurate value of overhydration that was an independent predictor of mortality in contrast to the ECW/total body water (TBW)
[22]. Different BIS parameters, such as ECW/TBW, ECW normalized for height, the OH value, and tissue hydration, have been used as indices of hydration in previous studies
[6, 9, 10]. In other words, there is no definite BIS parameter for assessing the hydration status. In this respect, the usefulness and relevance of BIS various parameters will be determined in the present study.

Based on normal hydration being defined as ECW within ±1.1 liter of the 10th to the 90th percentiles in healthy subjects
[10], previous studies for patients on HD have applied the same criteria
[23–25]. Although some studies have suggested cutoff thresholds for the definition of the OH in patients on HD and patients on PD of 2.5 and 2.0 liters, respectively
[19, 26, 27], we consider an ECW within ±1.1 liter as normal hydration.

There is a chance that patients within the same institution will be more correlated than patients between institutions. To avoid this, we will investigate for possible clustering of patients at the recruitment institution level, and will accommodate such clustering in our models and analysis as required. We also conservatively calculate the sample size, assuming a high drop-out rate, to overcome this potential problem.

A limitation of this study is that we will include both prevalent and incident patients on PD. Although a study targeting only incident patients on PD might provide more solid results, we will adjust the dialysis vintage in the multivariable analyses.

In summary, the COMPASS study is the first prospective, randomized controlled trial to evaluate the clinical usefulness of BIS-guided fluid management in patients on PD. The aim of this study is to evaluate whether BIS-guided fluid management has a beneficial effect on the decline of RRF, cardiac parameters, and cardiovascular outcomes.

## Trial status

This trial is ongoing. Participants are currently being recruited.

## Abbreviations

BP: Blood pressure
BIS: Bioimpedance spectroscopy
BWT: Body weight
CBC: Complete blood count
Cr: Creatinine
ECW: Extracellular water
GFR: Glomerular filtration rate
HD: Hemodialysis
hs-CRP: High-sensitivity C-reactive protein
ICW: Intracellular water
ITT: Intention-to treat
OH: Overhydration
PD: Peritoneal dialysis
PP: Per-protocol
PWV: Pulse wave velocity
RRF: Residual renal function
TBW: Total body water.
